### Sample Size

Sample size has been estimated based on previous multicenter controlled studies (21, 48). Under the assumption of normal distribution of the primary outcome scores and considering an α level of 0.05, a sample size of 60 subjects resulted in a power >70% and was then chosen for this trial.

### Data Collection

Assessments will take place at the Don Carlo Gnocchi Foundation (Florence, Italy). All assessors will receive proper instructions and guidance regarding all outcome parameters and assessments that will be taken. A reminder for each visit will be given to all patients to diminish retention and incomplete follow-up.

### Data Management

Study data will be recorded in an access database. All participants will be registered with an identification code with a random order. Source data will include the original documents relating to the study, as well as the medical treatment and medical history of participant. The database will be kept current to reflect subject status at each phase during the course of the study.

### Statistical Analyses

Statistical analysis on outcome measures will be conducted using SPSS version 24 (SPSS Inc, Chicago, IL). Baseline differences between groups will be tested by the independent-samples *t*-test for parametric data and the Mann-Whitney *U*-test for non-parametric data. According to data normality, a statistical test for independent samples will be performed to look at significant changes in primary and secondary outcome measures between control and treatment groups. Moreover, a statistical test for paired sample will be used to investigate the presence of significant changes in the treatment group cognitive and physical parameters before and after the tele-rehabilitation program. An alpha level of ≤ 0.05 will be considered as significant.

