## Abstract

**Background:** People living with Mild Cognitive Impairment (MCI) and Vascular Cognitive Impairment (VCI) are persons who do not fulfill a diagnosis of dementia, but who have a high risk of progressing to a dementia disorder. The most recent guidelines to counteract cognitive decline in MCI/VCI subjects suggest a multidimensional and multi-domain interventions combining cognitive, physical, and social activities. The purpose of this study is to test an innovative service that provides a multi-dimensional tele-rehabilitation program through a user-friendly web application. The latter has been developed through a participatory design involving MCI specialists, patients, and their caregivers. Particularly, the proposed tele-rehabilitation program includes cognitive, physical, and caregiver-supported social activities. The goal is to promote and preserve an active life style and counteract cognitive decline in people living with MCI/VCI.

**Methods:**The study is a randomized controlled trial. Sixty subjects will be randomly assigned to the experimental group, who will receive the tele-rehabilitation program, or the control group, who will not receive any treatment. The trial protocol comprises three steps of assessment for the experimental group: at the baseline (T_0), after tele-rehabilitation program (T_1) and at follow-up after 12-months (T_2). Differently, the control group will be assessed twice: at the baseline and at 12-months follow-up. Both the experimental and the control group will be assessed with a multidimensional evaluation battery, including cognitive functioning, behavioral, functional, and quality of life measures. The tele-rehabilitation program lasts 8 weeks and includes cognitive exercises 3 days a week, physical activities 2 days a week, and social activities once a week. In addition, group will be given an actigraph (GENEActiv, Activisinghts Ltd., Cambridgshire, UK) to track physical and sleep activity.

**Discussion:**Results of this study will inform on the efficacy of the proposed tele-rehabilitation to prevent or delay further cognitive decline in MCI/VCI subjects. The expected outcome is to counteract cognitive decline and improve both physical functioning and quality of life.

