
## Methods and Analysis

### Study Design

The proposed study is a randomized controlled clinical trial. A Consolidated Standards of Reporting Trials (CONSORT) flow diagram for enrollment and randomization in the GOAL study is showed in Figure 1. Subjects that, at the first screening will be deemed as eligible, according to the inclusion criteria, will undergo a baseline assessment (T_0). During the baseline a general cognitive and physical evaluation will be performed by using the scales, tests and questionnaires reported in the Participant's evaluation sub-paragraph. Participants will be then randomly assigned, through the use of a computer algorithm (http://www.graphpad.com/quikcalcs/randMenu/) to the control or treatment group. The tele-rehabilitation program will comprise the performing of cognitive exercises 3 days a week, APA activities 2 days a week, and social activities once a week. In addition, treatment group will be given an actigraph (GENEActiv, Activisinghts Ltd., Cambridgshire, UK) to track physical and sleep activity. Those subjects will undergo a post-training assessment immediately at the end of the tele-rehabilitation program (T_1) and after 12 months (T_2). Participants belonging to the control group will be evaluated only at T_2.

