**SECONDARY OUTCOMES:**			
**Activities of daily living inventory**	✓	✓	✓
•The Activities of Daily Living Inventory (ADCS-ADL) (37)			
**Depression symptoms**	✓	✓	✓
•The center for Epidemiological Studies Depression scale (CES-D) (38)			
**Health status**	✓		✓
•The 36-Item Short Form Survey (SF-36) (39)			
**Cognitive reserve**	✓		
•The cognitive Reserve Index questionnaire (CRIq) (40)			
**Physical activity level**	✓	✓	✓
•The short Physcal performance battery (SPPB) (41)			
•The Harvard Alumni Activity Survey (HAAS) (42)	✓		✓
•The International Physical Activity Questionnaire (IPAQ) (43)	✓		✓

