### Outcomes Measures

As the aim of this program will be to involve the participants in multidimensional activities to counteract cognitive decline, the primary outcome of this study will be the changes of cognitive domains evaluated (such as general cognitive assessment, memory, attention, and executive functions, visuospatial/constructional ability, and language) of the whole sample through a comprehensive neuropsychological assessment at T_0 and at T_2 (see Table 2 for a detailed list of the used neuropsychological tools). Together with the cognitive level, the following secondary outcomes will be evaluated in the whole sample at T_0 and T_2: independence, presence of depressive symptoms, quality of life and physical activity level through scales and actigraphic data (see Table 2 for the used questionnaires). In addition, the primary and secondary outcomes will be evaluated in the treatment group before and after the tele-rehabilitation program using a reduced battery of tests (see Table 2).

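### The between-arm test on T0–T2 changes is chosen by normality and has no baseline covariate; one pre-specified ANCOVA would generally be more precise and would fix what is estimated

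*Protocol article*

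**What the plan says.** Protocol article, Statistical Analyses: "According to data normality, a statistical test for independent samples will be performed to look at significant changes in primary and secondary outcome measures" between the control and treatment groups. The sentence names neither a specific test nor a covariate. The t-test and the Mann-Whitney test are named one sentence before, for another purpose: "Baseline differences between groups will be tested" with one or the other. It is a reasonable inference, but only an inference, that the same pair is meant for the outcome comparison.

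The Outcomes Measures section defines the quantity compared: "the primary outcome of this study will be the changes of cognitive domains evaluated" in the whole sample, from T0 to T2. Table 2 lists ten rows of cognitive measures under the primary outcome.

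On the availability of T0 scores, the Abstract states that "the control group will be assessed twice: at the baseline and at 12-months follow-up", and Study Design places the T0 assessment before randomisation. One sentence in Study Design reads differently: "Participants belonging to the control group will be evaluated only at T_2".

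The Sample Size section gives 60 subjects, an alpha of 0.05 and power above 70%. It gives no effect size, SD or T0–T2 correlation.

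**The concern.** Two features of the stated analysis deserve a change.

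The first is precision. A change score fixes the coefficient on T0 at exactly 1. Regression on T0 estimates that coefficient from the data and so removes at least as much of the variation that T0 explains. In a trial of 60 that claims only a little over 70% power, and that names small numbers and drop-out among its own limitations, precision available from data already collected is worth having.

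The second is that the analysis stays open until the data are seen. If normality decides between a t-test and a rank test, one cognitive measure may be reported as a difference in means and the next as a comparison of ranks. The results would then not share one estimand, and the section names no effect estimate to hold them together.

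**Working it through.** **Inputs from the protocol article.** N = 60, alpha 0.05, power above 70% (Sample Size); comparison of T0–T2 changes (Outcomes Measures, Statistical Analyses).

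**Assumptions, because the article gives no figure.** 30 per arm; two-sided test; power of exactly 70% for the change-score t-test; T0–T2 correlation r from 0.5 to 0.9; SD ratio k = SD(T2)/SD(T0) of 1, 1.2 or 1.3; no drop-out.

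**1. The plan's own figure.** Without an effect size and SD, the power above 70% can be neither reproduced nor refuted. Solving backwards with the noncentral t (58 df), 70% power at 30 per arm implies a standardised difference of d = 0.652 in SDs of the change score.

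**2. Variance formulas.** With SD(T0) = 1 and SD(T2) = k:

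- change score: 1 + k² − 2rk
- ANCOVA residual: k²(1 − r²)
- change score minus ANCOVA: (1 − rk)²

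The ANCOVA variance is therefore never the larger in large samples, and the two are equal when rk = 1. With equal SDs (k = 1), the ratio of ANCOVA to change-score variance reduces to (1 + r)/2.

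**3. Power after adjusting for T0.** The effect d is rescaled to 0.652/√(ratio × (1 + 1/56)), with 57 df. The factor 1 + 1/56 is the finite-sample cost of estimating the T0 slope.

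| r | ratio, k = 1 | power | ratio, k = 1.2 | power | ratio, k = 1.3 | power |
|---|---|---|---|---|---|---|
| 0.5 | 0.75 | 81% | 0.871 | 75% | 0.912 | 73% |
| 0.6 | 0.80 | 79% | 0.922 | 73% | 0.957 | 71% |
| 0.7 | 0.85 | 76% | 0.966 | 71% | 0.991 | 70% |
| 0.8 | 0.90 | 74% | 0.997 | 69% | 0.997 | 69% |

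At r = 0.9 and k = 1 the ratio is 0.95 and the power 71%.

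Example of a ratio: r = 0.7, k = 1.2 gives 1.44 × 0.51 / (1 + 1.44 − 1.68) = 0.7344/0.76 = 0.966.

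**4. Simulation check (k = 1, 20,000 trials per setting).** ANCOVA power was 81.1%, 76.4%, 74.4% and 71.5% at r = 0.5, 0.7, 0.8 and 0.9. Its type I error over all settings was 5.0–5.2%.

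**5. Cost of the diagnosis term.** The table adjusts for T0 only. If diagnosis were unrelated to outcome, adding it changes the factor to 1 + 2/55 with 56 df, and power at r = 0.5, k = 1 falls from 81.1% to 80.4%. The critical t moves from 2.0017 (58 df) to 2.0032 (56 df). If diagnosis predicts the T2 score, this is offset or reversed; the article gives nothing from which to size that.

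**6. Test switching.** Its effect on error rates was not quantified. The argument rests on the estimand alone.

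**The case against.** The strongest reply is that the planned test is sound. Arms are randomised, the change score is a legitimate outcome, and the gain from ANCOVA depends on two quantities that the article does not report. Entry requires an MMSE of at least 24, which may narrow T0 scores, and 12 months of uneven decline may widen T2 scores. With k around 1.2 to 1.3 and a high correlation, the gain disappears. This stands, and it is why the size is given as a range.

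A reader might infer more than the article supports:

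- *That T0 is ignored.* Both the outcome definition and the analysis sentence speak of changes, so T0 enters by subtraction. The much larger gain that ANCOVA has over a test of T2 scores alone does not apply.
- *That controls have no T0, so ANCOVA is impossible.* The Study Design sentence on controls, read literally, says so. The Abstract, Outcomes Measures and the order of baseline before randomisation say otherwise. Without a control T0 the planned comparison of changes would be equally impossible.
- *That randomisation is unstratified and should be changed.* The article says only that a computer algorithm is used. A condensed article may leave strata to the full protocol, so silence proves nothing.
- *That the Cognitive Reserve Index is to be analysed as an outcome.* It stands under the secondary heading of Table 2 with a T0 tick only, but Outcomes Measures does not list cognitive reserve among the secondary outcomes. This is a heading slip.
- *That the baseline significance tests do harm.* No decision is attached to them, so dropping them would change no result.

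It may also be said that a statistical analysis plan could add covariates. But the article states a method here; a plan using ANCOVA would replace that method, not fill a gap.

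**Conclusion.** The point holds as one of efficiency and pre-specification, not of validity. From an assumed 70% power at 30 per arm, adjusting for T0 adds about 11, 9, 6, 4 and 1 points at r = 0.5, 0.6, 0.7, 0.8 and 0.9 if the T0 and T2 SDs are equal. If the T2 SD is 20–30% larger, it adds about 0 to 5 points over r = 0.5–0.8. At worst in the range examined, the finite-sample penalty leaves T0-adjusted power just under 70% (69%). The correlation, SD ratio, allocation ratio and sidedness are all assumed.

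The second gain does not depend on those assumptions: a single named model gives every outcome the same kind of estimate, decided before the data are seen.

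**What to change.** Replace the between-arm sentence in Statistical Analyses with one pre-specified ANCOVA for each outcome measured at T0 and T2: T2 score on arm, T0 score and diagnosis (MCI due to AD or VCI). Report the adjusted mean difference with its 95% CI. For skewed scores, state in advance robust or bootstrap standard errors, or a named transformation, in place of choosing the test by normality. Fix the covariates in the text, so that analyst choice does not return by another route.

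Reconcile the Study Design sentence on control-arm assessments with the Abstract and Outcomes Measures, so that it is clear that controls contribute a T0 score.

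The cost is rewording and two degrees of freedom. No patients, visits or instruments are added: the T0 score is already planned and diagnosis is an entry criterion. SPSS, the package already named, fits the model.

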## Discussion And Conclusions

In the context of cognitive decline, technologies have been increasingly conceived as a support for patients, their caregivers and the clinicians. The presented trial is claiming to provide MCI/VCI subjects together with their caregivers with an innovative customized tele-rehabilitation program, which contents are available by a user-friendly web application. However, the lack of familiarity with the technologic devices may constitute a limit to the implementation of technology enhanced services to supply a home-based tele-rehabilitation in people with advanced age or early cognitive impairment (23). For this reason, the use of a participatory co-design process that follows an iterative development model might help in overcoming this limitation. The following challenges to program implementation were successfully managed:
- Define the program contents most likely to offer a multi-domain and multi-dimensional stimulation;- Develop a platform to enable the participants self-administration of the program contents at home;- Create a user-friendly interface platform to ease a possible lack of familiarity with technology.

The first challenge has been addressed by creating a weekly program that combines cognitive and physical, similar to what has been proposed by Realdon et al. (21). Differently from their project, the physical activity proposed in this program is based on APA exercises and customized to the participant's training level and physical capability. In addition, this program promotes the participation of the subjects in social activities to be conducted with the support of the caregiver. The choice to include in the training program social activities originates from evidence in the literature showing the importance of social stimulation as protective factor against major cognitive decline (17, 49). The second challenge has been met by creating a web-app and providing participants with a tablet and an internet connection, if needed. The possibility to perform the exercises at home, will likely enhance participation in the program. Furthermore, the proposed tele-rehabilitation program leads to a significant reduction of costs compared to previously proposed trainings (50, 51), where participants attended a clinic and were supervised by medical staff. The third challenge has been dealt through a participatory co-design process, used to develop a platform shaped on the basis of user needs. The possible limitations of this study may stem from the restricted numbers of participants enrolled. A potential pitfall could be a drop-out of MCI, therefore the sample size will be increased. Data collection may be impacted by the adherence to the program, especially considering the age of participants, their compliance to the treatment and their medical condition. The monitoring of activity by the administrator is among the several strategies expected to help solve the possible problem of the adherence. However, a high adherence is expected due to the possibility to carry this out at home. To protect sensitive data that will be stored and processed through the web-application, all participants will be registered with an identification code with a random order. Another limitation could be a potential learning effect of neuropsychological instruments due to the timing of the project. This could be avoided by using parallel versions when possible and by a well-structured time scheduling. Some symptoms of apathy, a predictive factor of AD progression (52, 53), are indirectly tested by registering daytime motor activity with actigraphic measures (54, 55). Direct specific measures of apathy cannot be used because of administration issues. The next step is to test the proposed program on subjects living with MCI and VCI condition through the presented trial. The expectation is to counteract cognitive decline, improve physical functioning and quality of life.

## Ethics And Dissemination

The study will be carried out in compliance with the protocol approved by the previously mentioned ethical committee. A written informed consent will be given to each participant (Appendix A in Supplementary Material). The trial is registered at https://clinicaltrials.gov, unique identifier NCT03383549 (registration date: 26/dec/2017). Potentially eligible participants will be screened by the study site principal or sub-investigator for the confirmation of a diagnosis of MCI due to AD or VCI, with a MMSE score ≥24 (26), an age between 65 and 80 years old, a school attendance ≥3 years and with a right-dominant hand. Additionally, potential participants will be questioned and their medical record will be checked in regard to the other eligibility criteria. Given eligibility to take part in the study, they will be provided with further details and an informed consent form by one of the study members. The model consent form and other related documentation given to participants (all in Italian) can be obtained by the corresponding author upon request. The study clinicians will be responsible to explain and make sure the protocol is correctly understood by participants. A separate list with patients screened, but who are not enrolled will contain information regarding the number of patients and the reasons for not enrolling. In order to provide an equal and ethic treatment to all participants, the control group will receive the proposed program at a later date. All anonymized data will be stored in a secure database protected by a password. Only the research team will have access to the database. After the statistical analysis of this trial, the data will be published in a peer-reviewed medical journal, thereby adhering to the CONSORT reporting standards (56) and SPIRIT guidelines (57). The results will be disseminated through peer-reviewed publications, presentation at relevant scientific conferences and the general public.

## Ethics Statement

This study was approved by the Ethical Commitee of IRCCS Don Carlo Gnocchi Foundation and is registered as a clinical trial (NCT03383549). Prospective participants will be fully informed of the aims and procedures of the project. A reporting procedure will be in place to ensure that any serious adverse events are reported to the Chief Investigator. Informed consent will be obtained from all participants and their caregivers before the study initation.
